
## Section G: Sample Size/Data Analysis

### G1. Sample Size

How many subjects (or specimens, or charts) will be used in this study?

Local: 455      Worldwide: 455

Please indicate why you chose the sample size proposed:

The proposed sample size of 455 includes 425 patients and 30 clinicians.

The sample size of clinicians was determined by creating a schedule for the expected flow of Veteran participants in the study that predicts expected demand for coaching.

In determining the sample size of patients for the study, we examined the number of patients needed to have adequate power for both hypotheses related to the primary aim (specific aim 1). The sample size determined for the primary aim was inflated to account for potential correlation of patients treated by the same PCP and to account for attrition at 1 year of 25%, based on our and other prior VA studies.

The sample size is based on testing for a clinically important difference between the two groups at a single time point, using a two-group t test with a 0.05 two-sided significance level and power of 80%. For HbA1C, a difference of 0.5 is considered clinically significant within a 6-month time frame. Using a difference score of 0.5 in the mean HbA1c between the two groups and an estimated pooled standard deviation of 1.1 results in

an effect size,  $d = .45$ . This effect size is consistent with our prior RCT study on behavioral coaching interventions which generated HbA1c level differences of 0.68 and a medium effect size of 0.50 and estimates from our HOPE pilot confirm these effects. Using these data, a sample size of 79 per group or 158 total would be needed for a significant difference in the proportion of participants achieving greater than or equal to 0.5 improvement in HbA1c.

For PHQ-9, a score of less than 10 or a 5-point decline from baseline would be considered a clinically significant improvement. The sample size of 79 per group would have 80% power to detect a change as small as 1.5 points in the PHQ-9 score with a two-sided  $\alpha = 0.05$ . From our own work using cognitive-behavioral therapy for medically ill Veterans with depression, we found clinically significant improvements in Beck Depression Scale scores consistent with effect sizes of 0.98 at 8 weeks and 1.05 at 20 weeks post-intervention. This level of efficacy is consistent with our estimates of clinically significant change as indicated by PHQ-9 scores.

Following the approach of Schnurr et al, we inflated the sample size to account for a correlation among patients seen by the same PCP using the formula,  $f = 1 + (m - 1)\bar{r}$ , where  $m$  is the average number of patients per provider and  $\bar{r}$  is the intra-class correlation coefficient. Assuming there will be 40 to 50 PCPs results in  $m = 4$  and estimating  $\bar{r}$  as .05 yields  $f = 1.15$ . This inflation factor is modest but reasonable, given the nature of the study and the extent of the external clinical providers' involvement (supported by personal communication with [name] – May 2010).

Thus, the sample size needed for analysis is 182 total (91 per group). Finally, adjusting this for 25% attrition using the inflation factor of 1.33 [i.e.,  $1/(1-.25)$ ] gives a total of 242 patients to be recruited. Therefore, a final cohort of 182 at 12-month follow-up (i.e., recruitment of 242 to allow for 25% attrition) would provide sufficient power to conduct analyses for Aim 1. This sample would provide 80% power to detect an effect size of 0.45, which represents a difference in HbA1c of 0.5 with a standard deviation of 1.1 and a difference in PHQ-9 scores of as little as 1.5 with standard deviation of 3.4.

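### G1 attaches the 79-per-group figure to a responder proportion, but 79 is the t-test size for a difference in mean HbA1c; the responder comparison would have roughly 60% power

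*Protocol*

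**What the plan says.** G1 sets out the sizing as a comparison of means, "using a two-group t test with a 0.05 two-sided significance level and power of 80" per cent. The inputs are given as "Using a difference score of 0.5 in the mean HbA1c between the two groups and an estimated pooled standard deviation of 1.1", which the protocol turns into d = .45.

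The result is then attached to a different quantity: "a sample size of 79 per group or 158 total would be needed for a significant difference in the proportion of participants". The proportion meant is the share of patients whose HbA1c falls by 0.5 or more. No response rate is stated for HOPE or for enhanced usual care (EUC).

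After the inflation for clustering and attrition, G1 returns to means: "This sample would provide 80% power to detect an effect size of 0.45", explained there as a 0.5 HbA1c difference with SD 1.1.

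G2 makes the continuous HbA1c and PHQ-9 values the primary outcomes, analysed by hierarchical linear models adjusted for baseline value, insulin use and site, among other variables. It adds a hierarchical logistic regression of the dichotomised outcomes, with an HbA1c decrease of 0.5 as the threshold.

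In support of the effect size, G1 cites a prior behavioural coaching trial "which generated HbA1c level differences of 0.68 and a medium effect size of 0.50" and adds that "estimates from our HOPE pilot confirm these effects". It reports no SD for either study.

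**The concern.** A sample size for a difference in means does not carry over to a difference in the proportion crossing a threshold. Dichotomising discards information, so the same underlying shift needs more patients. A size for proportions also needs two response rates, and the protocol has none. The sentence therefore contradicts the text before and after it in G1.

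This matters because the responder analysis will be run. A reader who takes the G1 sentence at face value would treat a non-significant responder result as coming from a test with 80% power, and so as fair evidence against a clinically meaningful benefit. If power is nearer 60%, that reading is too strong.

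**Working it through.** **1. Reproduce 79.** Inputs from G1: difference 0.5, SD 1.1, two-sided alpha 0.05, power 80%.

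- d = 0.5/1.1 = 0.4545, stated as .45.
- Normal approximation: n = 2(1.96 + 0.8416)²/0.45² = 15.70/0.2025 = 77.5, so 78 per group.
- Noncentral t at d = 0.45: n = 78.5, so 79 per group, with power 80.3% at 79.

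The stated figure is exactly the t-test size for means. The later steps also follow: 158 × 1.15 = 181.7, so 182; 182 × 1.33 = 242.

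**2. Power of 79 per group for the responder proportion.** The protocol gives no rates, so they must be assumed. I take change in HbA1c as normal with SD 1.1, a true mean difference of 0.5, and EUC mean improvement m from -0.25 to 0.75. Then

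- EUC rate = 1 - Φ((0.5 - m)/1.1)
- HOPE rate = 1 - Φ((0.5 - m - 0.5)/1.1)
- power = Φ{(p₁ - p₀ - 1.96·s₀)/s₁}, with s₀ the pooled and s₁ the unpooled standard error.

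Example at m = 0: rates 0.325 and 0.500, pooled rate 0.4125. s₀ = √(0.4125 × 0.5875 × 2/79) = 0.0783 and s₁ = √((0.325 × 0.675 + 0.25)/79) = 0.0771. Then (0.175 - 1.96 × 0.0783)/0.0771 = 0.28, and power is Φ(0.28) = 0.61.

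For the planned allocation (60:40 in F1), 182 analysed patients split as 109.2 and 72.8. Divided by the design factor 1.15, these become effective sizes of 95.0 and 63.3.

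| EUC mean improvement | EUC rate | HOPE rate | Power, 79 per group | n per group for 80% | Power, 60:40 |
|---|---|---|---|---|---|
| -0.25 | 24.8% | 41.0% | 58.6% | 131 | 56.0% |
| 0 | 32.5% | 50.0% | 61.1% | 123 | 59.0% |
| 0.25 | 41.0% | 59.0% | 62.0% | 121 | 60.3% |
| 0.50 | 50.0% | 67.5% | 61.1% | 123 | 59.9% |
| 0.75 | 59.0% | 75.2% | 58.6% | 131 | 57.8% |

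A 0.5 shift in the mean moves the response rate by 16 to 18 percentage points. For 80% power, 79 per group would need, for example, 30% against about 52%.

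**3. Sensitivity of the means comparison to the SD.** The cited trial's two figures imply an SD of 0.68/0.50 = 1.36.

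- If that SD applied unadjusted, a 0.5 difference would be d = 0.5/1.36 = 0.368. Power would be 63% at 79 per group and about 61% at the 60:40 effective sizes.
- If 1.36 is an unadjusted SD, adjusting for a baseline with correlation r reduces it to 1.36·√(1 - r²). At r = 0.5 this is 1.18, with power 76% at 79 per group; at r = 0.6 it is 1.09, with power 82%. The correlations are assumed.
- At the cited trial's own d of 0.50, 79 per group gives 88%.

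**The case against.** The best defence is that one sentence is badly worded and nothing else is affected. The test named is a t test, the inputs are a mean difference and an SD, the closing statement of G1 is correct, and G2 makes the continuous outcomes primary. All of that stands: 79, 182 and 242 reproduce on the stated inputs. It does not rescue the sentence itself, which ties a stated size to an endpoint that G2 goes on to analyse.

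It is also fair to say that the figure of about 60% rests on assumptions from outside the protocol: normal change, SD 1.1 read as the SD of change, and a simple two-proportion test in place of the covariate-adjusted hierarchical logistic model. It is an illustration. It is nevertheless stable over the range of EUC improvement shown, and no response rates are offered that would give a different answer.

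A reader might go further and infer from the implied SD of 1.36 that the trial's main HbA1c comparison really has about 60% power. The protocol does not support that. It cites the prior trial for the effect size, and a planned 0.45 is consistent with, and slightly below, an observed 0.50. The 63% figure pairs the smaller planned difference of 0.5 with an SD back-calculated from a trial that observed 0.68. Whether the 0.50 was standardised by a final-value, change or adjusted SD is not stated, the pilot SD is not reported, and the primary model adjusts for baseline.

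**Conclusion.** The sentence in G1 is wrong as written. The figure of 79 per group gives 80% power for a 0.5 difference in mean HbA1c at SD 1.1. For the proportion improving by at least 0.5, power would be about 59-62% at 79 per group, or about 56-60% at 60:40 with 182 analysed and the clustering factor applied, under normal change with SD 1.1 and EUC mean improvement from -0.25 to 0.75. About 121 to 131 per group would be needed for 80%, before inflation.

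The fault is confined to the claim about the responder analysis. The calculation for the primary comparison of means is reproduced on the protocol's own inputs, and the statement that d = .45 is consistent with the prior trial may stay. The SD of 1.36 is a conditional sensitivity and does not show that 1.1 is wrong.

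**What to change.** In G1, reword the sentence to say that 79 per group gives 80% power to detect a 0.5 difference in mean HbA1c at SD 1.1. In G2, describe the dichotomised HbA1c analysis as supportive, with roughly 60% power under stated assumptions. Alternatively, give the response rates that would justify 79 for that endpoint.

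Optionally, state where SD 1.1 comes from (for example, whether it is a baseline-adjusted residual SD) and add one sensitivity line: at an unadjusted SD of 1.36, power for a 0.5 mean difference would be about 63% at 79 per group and about 61% at 60:40, with baseline adjustment recovering some of it.

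These are changes of text only. Enrolment, the primary outcomes and the primary model are untouched. The cost is a less favourable stated power for the responder analysis.

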## G2. Data Analysis

Provide a description of your plan for data analysis. State the types of comparisons you plan (e.g. comparison of means, comparison of proportions, regressions, analysis of variance). Which is the PRIMARY comparison/analysis? How will the analyses proposed relate to the primary purposes of your study?

Data Collection Strategy: Data will be collected by self-report, chart review, and laboratory collection.

Independent Evaluators (IE) who are blinded to the study procedures and treatment assignments will collect data at 6 and 12 months by phone. They will mail assessment packets to participants and then work with them to complete all self-report items. IEs will arrange a lab visit for a blood draw within 2 weeks before and 2 weeks after the target data-collection time (facilitated by PCPs). If PCPs have already obtained A1c levels in that timeframe, those values will be used. Participants will receive modest compensation after A1c results and self-report assessments are collected. RAs will also perform chart abstraction of clinical baseline, moderating, and exploratory variables. Data Quality Assurance: Using previously developed and standardized procedure manuals, providing rigorous training and fidelity measurement of study coaches and independent evaluators, as well as providing written guides for assessments are ways quality will be assured. Attrition/Retention and Missing Data: We expect rates of missing data for primary outcomes less than 25%, leading to primary outcome data for greater than 75% of participants. To evaluate the potential relationship between loss to f/u and outcome variables, reasons for study discontinuation will be recorded for subsequent analyses, and overall attrition rates will be factored in the analyses of the primary specific aim. We will conduct sensitivity analyses using tests for data missing completely at random and tests for nonrandom missingness. We will also plot the data over time to visually assess changes in outcomes from baseline to 12 mos. and to indicate whether additional terms are needed in the models to account for nonlinearity over time. Data Analysis Plan: Primary Analyses: A1c and Depression Outcomes--We will compare participants in the two study arms on baseline characteristics, including sociodemographic characteristics (age, race/ethnicity, gender, education level, independent living status, VA copay status, employment status) and clinical variables (BMI, Deyo comorbidity score, psychotropic and diabetes medications and treatments, specific psychiatric diagnoses, and number of PCP visits in the previous 12 mos). Based on recommendations of the CONSORT group, we will not provide tests of significance or adjust subsequent analyses for variables found to differ because adjustment may bias the estimated treatment effect. However, the analyses for the primary aim will be adjusted for variables we have decided a priori may be important to control: a) baseline values of HbA1c and PHQ-9, b) whether the patient was on exogenous insulin, and c) the stratification variable, site. In addition, we will compare participants on d) access to psychotherapy and medication, defined as dichotomous variables. At baseline, 6 months, and 12 months, we will construct variables for whether the patient was receiving

psychotherapy during the previous 6 months (yes/no), whether psychotropic medications were started or changed during the past 6 months (yes/no), and whether insulin was added during the past 6 months (yes/no). A1c and Depression Outcomes at 6 months--The patients' A1c levels and PHQ-9 scores at 6 months will be the primary outcomes. We will examine the normality of the distributions of these outcomes and will consider transformations such as the log or the inverse, if necessary. Separate models will be run for HbA1c and for PHQ-9. We will run hierarchical linear model analyses to account for the correlation of patients being seen by the same PCP. Using this nested approach, we will test if there are differences between EUC and the HOPE intervention, using the A1c level and the PHQ-9 score (either untransformed or transformed, if needed) as dependent measures. Although patients are also nested within coach, the coaches are not assigned exclusively to certain PCPs. We will include intervention fidelity scores for each coach as a study variable in our analysis of this aim to account for coaching fidelity effects. Each model will contain a variable indicating the treatment group, indicator variables representing site, whether or not the patient was on exogenous insulin (evidence suggests that insulin use impacts both A1c and depressive symptoms), receiving psychotherapy, taking psychotropic meds, and baseline A1c or PHQ-9 levels as independent variables. A significant value for the treatment group variable in the hierarchical model will indicate that there were statistically significant differences between the intervention and EUC. In addition, we will examine whether the groups differed as to whether or not they had clinically significant changes in A1c and PHQ-9 by dichotomizing the outcomes. A significant decrease for A1c is defined as 0.5 between each time point and from baseline to 12-months. For PHQ-9, this will be a change score of 5 or greater at 6- and 12-months. We will test whether the two groups (clinically significant change vs. no change) differed using a hierarchical logistic-regression model in which the dichotomous outcomes are the dependent variable. The independent variables will be those described above for the hierarchical linear regression. A1c and Depression Outcomes at 12-months-- The patients' A1c levels and PHQ-9 scores at 12-months will be the primary outcomes. Similar to the analyses at 6 months, we will examine the distribution and run hierarchical linear models on the 12 month data. In addition, we will examine all of the time periods in a hierarchical longitudinal analysis, separately for A1c and PHQ-9. This random coefficient model will allow us to fit a line for each participant using his/her available data, including participants with missing values, and will maximize the power to detect differences because patients are not removed from the analysis if any of the time periods is missing. Patients will be nested with their PCP. The model will contain the A1c and PHQ-9 values for each of the time periods (baseline, 6 and 12 months). The independent variables in the model will be time, treatment, the interaction of time and treatment, site, and use of exogenous insulin psychotropic meds, or psychotherapy. The treatment effect will measure differences between the intervention and EUC groups at baseline, and the time effect will measure whether there was an overall change over time in the two clinical outcomes. The time-by-treatment interaction is of most interest in the longitudinal analysis because a significant value will indicate that there was a difference between the intervention and EUC groups over the 12-month time period. Mediators and Moderators: To examine the role of potential moderators and mediators on intervention effectiveness, we will evaluate factors that mediate and moderate outcomes at 6 and 12 months. Moderating variables are those that specify on whom and under which conditions treatments have different effects. The moderating variables for this aim include sociodemographic traits, BMI, medical and psychiatric comorbidity, and social support. Mediator variables identify possible mechanisms through which a treatment achieves its effect. Mediators include the GET-D scores for goals and action plans, diabetes-related distress, self-efficacy, performance of self-care behaviors, and adherence to pharmacological therapy. We will consider the difference between the moderators and mediators in terms of when they occur relative to treatment and whether they are correlated with treatment. Moderators must precede treatment and should not be correlated with treatment. Mediators will occur during treatment and should be correlated with treatment. Thus, we will initially test for the association of the moderating and mediating variables with treatment. Since the treatment is a dichotomous variable, we will use t tests to determine if continuous moderators or mediators are associated with treatment and chi-square tests to determine if ordinal or categorical moderators or mediators are related to treatment. After verifying that a possible moderator is not significantly related to treatment, we will run the model, including a term in the model for the moderator and a term for the interaction of that variable with treatment. A significant value for the interaction term will indicate that the effect of treatment on the individual patients depends on their value of the moderator. For mediators, we will test if the variable has either a main or interactive effect on the outcome. With an emphasis on the effect size of treatments and what influences the effect size for a particular moderator or mediator, we will calculate effect sizes at each of the scheduled time points. In addition, we will form response categories to assess the stability of variables under two approaches to measuring outcomes (one using continuous variables for outcomes and the second using categories for the outcomes). For example, we might define an improvement in A1c as a decrease of 0.5 from baseline or PHQ-9 decrease of 5 from baseline. We would then run the analytic models using the dichotomous variable of whether or not the patients' A1c level improved as the outcome variable. If the two-variable presentations prove to be similar, we will likely use the categorical approach because of greater ease in reporting results to

clinicians based on response categories. Evaluating the potential for embedding the HOPE intervention within VA (Assessing Implementation): Exploration of reach--We will compare the demographic and clinical characteristics of study participants from the study sites to those of potentially eligible patients typically cared for at each CBOC and the MEDVAMC. For each site, we will test whether patients who participated differed from (a) patients who were approached but refused enrollment and (b) all remaining patients who would have met inclusion criteria but who were not included in the study, using analysis of variance for continuous variables and chi-square tests for categorical variables. The variables of interest will include age, gender, race, BMI, Deyo comorbidity score, and presence of PTSD or major depression. These variables will be obtained from the VISN 16 data warehouse. The potentially eligible patients cared for at each facility will be determined using diagnoses of diabetes and depression from the inpatient and outpatient files and A1c values from the VISN 16 data warehouse (with IRB approval). Exploration of adoption--We will evaluate the perceptions and practices of clinicians regarding intervention processes including the incorporation of behavioral goals and action plans within the progress notes and treatment plans described by PCPs. To accomplish this aim, we will purposively sample PCPs at each clinical site, including those who have cared for control and intervention subjects. We will use respondents' PACIC scores to purposively sample low and highly rated PCPs on the patient engagement and goal-setting subscales. Recruited PCPs will be evaluated using in-depth interviews to elicit their perceptions of the overall intervention procedures and their use of any constituent elements of each intervention. Consistent with established qualitative interview methodology, interviews will be audiotaped, transcribed, and analyzed using a deductive approach based on a coding system developed from our interview guide. Coded units will be reexamined for relationships and clustered into patterns. Based on past experience, we anticipate that each interview will last 30 minutes. Quantitative analyses will also be done on the coach surveys completed pre-, post-, and 6-months-post-training to assess change over time. The results of these quantitative and qualitative analyses will guide future implementation studies of the HOPE intervention in usual VA care.

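### The stated missing-data sensitivity analyses are tests of the missingness mechanism, so they do not show how far the HbA1c and PHQ-9 effects depend on the missing-at-random assumption

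*Protocol*

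**What the plan says.** Everything on this point is in the protocol, section G2 (Data Analysis), with the attrition allowance in G1 (Sample Size).

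- **Expected loss.** "We expect rates of missing data for primary outcomes less than 25" per cent. G1 uses 25% as the one-year attrition allowance. No separate figure is given for 6 months.
- **Sensitivity analysis.** "We will conduct sensitivity analyses using tests for data missing completely at random and tests for nonrandom missingness". No test is named, and nothing is said about what follows from its result.
- **Use of attrition data.** "reasons for study discontinuation will be recorded for subsequent analyses, and overall attrition rates will be factored in the analyses of the primary specific aim". The way attrition is to enter those analyses is not described.
- **Primary models.** "The patients' A1c levels and PHQ-9 scores at 6 months will be the primary outcomes"; the 12-month values are treated likewise. Each is analysed by a hierarchical linear model adjusted for baseline value, site, insulin use and mental health treatment.
- **Longitudinal model.** A random coefficient model will "fit a line for each participant using his/her available data, including participants with missing values".

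**The concern.** A sensitivity analysis for missing data estimates the treatment effect again under a different assumption about the unseen values. A test of the mechanism gives a p-value about the pattern of missingness and leaves the estimate where it was. G2 offers the second under the name of the first.

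The distinction matters because the troublesome case is the one that such tests cannot settle. Under MNAR, missingness depends on the unseen outcome even after allowing for what was observed. A non-significant MCAR test is therefore no evidence that MAR holds. A significant one shows dependence on observed data, which the planned models may already accommodate.

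Differential loss is plausible here. Under F2 (Procedure), HOPE patients have nine coaching calls in 6 months, while EUC patients have no further contact in the acute period. If those lost from one arm differ from those lost from the other in ways not captured by the observed data, both primary effects could be biased, and nothing specified in G2 would show by how much.

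**Working it through.** **1. The plan's own figures.** G1 sizes the trial "using a two-group t test with a 0.05 two-sided significance level and power of 80" per cent, with the inputs "Using a difference score of 0.5 in the mean HbA1c between the two groups" and "an estimated pooled standard deviation of 1.1".

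- Two-sample t test at the stated d = 0.45: 78.5, so 79 per group, 158 in total. (The unrounded 0.5/1.1 = 0.4545 gives 77; the 79 comes from rounding d.)
- Clustering: 1 + (4 − 1) × 0.05 = 1.15, and 158 × 1.15 = 181.7, so 182.
- Attrition: 182 × 1.33 = 242.06, so 242.

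The figures reproduce. The sample size replaces lost patients in number; it does not address whether they differ from those who stay.

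**2. What each element of G2 delivers.**

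| Element | Re-estimates the effect? | Covers departures from MAR? |
|---|---|---|
| MCAR tests | No | No; can show dependence on observed data |
| Tests for nonrandom missingness | Not as worded | No, without untestable assumptions |
| Recording reasons for discontinuation | No | Informative, but no estimate |
| Factoring in attrition rates | Method not stated | Cannot be judged |
| 6- and 12-month hierarchical models | Primary estimate | No; rely on MAR given the covariates |
| Random coefficient model | Yes, using all visits | No; relies on MAR |

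**3. Size of a departure (illustration).** Inputs from the protocol: 146 HOPE and 96 EUC (F1), effect 0.5, SD 1.1, design effect 1.15. Assumptions made here: 25% missing in each arm, the planned effect is what a MAR analysis estimates, and only missing HOPE patients do worse than MAR implies, by δ.

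- Observed: 146 × 0.75 = 109.5 and 96 × 0.75 = 72.
- SE = 1.1 × √[1.15 × (1/109.5 + 1/72)] = 0.179.
- Smallest significant difference = 1.96 × 0.179 = 0.351.
- Estimate = 0.5 − 0.25 × δ.

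| δ (HbA1c points) | Estimate | Share of 0.5 kept |
|---|---|---|
| 0 | 0.500 | 100% |
| 0.5 | 0.375 | 75% |
| 1.0 | 0.250 | 50% |
| 1.1 (one SD) | 0.225 | 45% |
| 2.0 | 0 | 0% |

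Significance is lost at δ = (0.5 − 0.351)/0.25 ≈ 0.60, about half an SD (0.60/1.1 = 0.54). With 91 per group the figure is 0.63. At δ = 0.5, where the missing HOPE patients gain nothing over EUC, the result remains significant: 0.375/0.179 = 2.10.

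For PHQ-9, with G1's effect of 1.5 and SD of 3.4, SE = 0.553 and the smallest significant difference is 1.084. Significance is lost at (1.5 − 1.084)/0.25 ≈ 1.7 points (1.8 with 91 per group).

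**4. Range over the missing fraction.** At an assumed 15% missing in each arm, 124.1 and 81.6 are observed. The HbA1c SE is 1.1 × √[1.15 × (1/124.1 + 1/81.6)] = 0.168, the threshold is 0.330, and the tipping point is (0.5 − 0.330)/0.15 ≈ 1.1, one full SD. If both arms depart by the same δ with equal missing fractions, the shifts cancel and the difference does not move.

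**5. Can observed data miss such a bias?** A simulation with 146 and 96 patients, about 25% missing, and HOPE dropout made to depend only on the part of the outcome unrelated to baseline gave a mean observed difference of −0.74 against a true −0.50. Comparing baseline values of missing and observed patients rejected in 5.4% of runs, the nominal rate. That result follows from the assumption made. It shows that such a bias can go unseen, not that it will occur here.

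**The case against.** The best case for the plan has four parts.

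**The detail belongs in the SAP.** Imputation models and delta grids do, and their absence here is no fault. But G2 does not leave the matter open: it names the kind of sensitivity analysis, and the kind is wrong for the purpose.

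**The wording may cover more.** Tests for nonrandom missingness could be meant to include pattern-mixture or selection models, which would re-estimate the effect. The text does not say so. If that was the intention, saying so is most of the fix.

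**Missing data are not ignored.** This stands. Reasons for discontinuation are recorded, and the random coefficient model gives a second estimate that uses incomplete records. Both estimates still rely on MAR.

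**The loss may be small and balanced.** This also stands in part. The 25% is an upper expectation. Stopping coaching is not the same as missing the outcome: blinded evaluators separate from the coaches collect the data, and G2 accepts HbA1c values already obtained by the PCP within the window. F2 also reports that HbA1c collection exceeded survey collection in a prior study. These points favour HbA1c more than PHQ-9, which must be collected from the patient.

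A reader might go further and infer that the tests detect nothing, that they have low power, or that the trial would pass its own check and report a biased effect. The protocol supports none of these. MCAR tests do detect dependence on observed data, no power can be calculated for an unnamed test, G2 sets no pass or fail rule, and there is no evidence that dropout will be informative.

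**Conclusion.** The concern holds as a poorly chosen stated method. G2 labels tests of mechanism as sensitivity analyses; they cannot separate MAR from MNAR and, as worded, do not re-estimate the effect. Nothing else specified in the protocol does so under a departure from MAR. It is not a finding that the results will be biased.

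The possible size is moderate. At the protocol's upper expectation for missing data, a departure of about 0.6 HbA1c points or 1.7 PHQ-9 points, each about half an SD and confined to missing HOPE patients, would remove significance from the planned effects. This rests on 25% missing in both arms, the planned effects holding under MAR, a design effect of 1.15, no gain in precision from baseline adjustment, and no departure in EUC. Relaxing the first or last of these makes the results sturdier: the HbA1c tipping point is about 1.1 at 15% missing, and equal departures in both arms cancel.

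**What to change.** In G2, with detail in the SAP:

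1. State MAR, given the variables in the model, as the primary missing-data assumption.
2. Replace the tests, as the sensitivity analysis, with a re-estimation of the 6- and 12-month HbA1c and PHQ-9 effects under departures from MAR. Delta-adjusted multiple imputation is one suitable method: vary δ separately by arm (for HbA1c, for example, 0, 0.25, 0.5 and 1.1 points, with matching SD fractions for PHQ-9) and report the tipping point. Reference-based imputation or a stated pattern-mixture or selection model would also serve.
3. Keep the MCAR tests, the comparison of completers with dropouts, and the reasons for discontinuation as description, and report missing fractions by arm and visit.
4. Say how attrition rates enter the primary analyses, or delete that phrase.

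The cost is revised wording and a modest amount of extra analysis. Sample size and data collection do not change.
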